### Patients

#### Study population and sample size

This study focuses on women experiencing perimenopausal syndrome. According to the previous study by Guang’anmen Hospital, China Academy of Chinese Medical Sciences (results still unpublished), the improvement of Menopause Rating Scale (MRS) scores of the electro-acupuncture group and the sham acupuncture group were 6.5 and 2, respectively. The difference in scores between the two groups was 4.5, and electro-acupuncture was not superior to sham acupuncture. Accordingly, we assume that a difference within 4.5 indicates acupuncture is not inferior to Climen® treatment. Using a non-inferiority design, and assuming a power of 90%, an alpha value of 5%, and a population standard deviation of 10, a total of 206 patients will be needed in this study. Each group needs 103 patients (assuming a 20% dropout rate).

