### Statistical analysis

All data from this study will be analyzed by special analysts with SPSS 20.0 (IBM Corp., Armonk, NY, USA).

The tests of outcomes are based on the intention-to-treat population. Sensitivity analyses are performed for the primary outcomes (MRS measured 16 weeks after randomization) by replacing missing data with multiple imputations and lost observations carried forward using SPSS 20.0. Multiple imputations are calculated using the propensity score method. The MRS is used as a dependent variable in an analysis of covariance, with the groups as random factors, and with baseline MRS and age as covariates, to account for potential baseline differences. Adjusted mean treatment effects are given alongside corresponding 95% confidence intervals and *P* values. The same analysis method will be performed for all secondary outcomes.

In addition to the above analysis, we will perform an exploratory analysis to describe group means over time. We will calculate summary statistics to reveal whether the two groups are changing in a similar or different fashion. A two-sided test is applied for available data, and *P* < 0.05 is considered statistically significant.

There is one acupuncturist in each center to do all treatment, which probably introduces a clustering effect in this trial. We therefore calculated the intracluster correlation coefficient from the result of this trial and report the coefficient [28].

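### The two named sensitivity analyses for week-16 MRS can bias towards non-inferiority, and neither is designed to count against acupuncture

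*Protocol article*

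**What the plan says.** All references are to the protocol article.

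- **Design** (Study population and sample size): the trial is sized for non-inferiority: "we assume that a difference within 4.5 indicates acupuncture is not inferior to Climen® treatment". The inputs are "assuming a power of 90%, an alpha value of 5%, and a population standard deviation of 10". Dropout enters as "Each group needs 103 patients (assuming a 20% dropout rate"; it is not split by arm or visit.
- **Analysis** (Statistical analysis): tests use the intention-to-treat population. MRS is analysed by analysis of covariance with baseline MRS and age as covariates, and "Adjusted mean treatment effects are given alongside corresponding 95% confidence intervals".
- **Missing data** (same section): the sensitivity analyses concern MRS at week 16 and consist of "replacing missing data with multiple imputations and lost observations carried forward using SPSS 20.0". On the imputation model the article adds only this: "Multiple imputations are calculated using the propensity score method". It does not say whether imputation is done within arm, or whether arm enters the score.
- **Timing** (Study design; Outcome measurement): treatment ends at week 12. MRS is taken at randomization and at weeks 4, 12, 16, 24 and 36.

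I read the carried-forward method as last observation carried forward (LOCF). No named analysis makes a pessimistic assumption about patients who leave the acupuncture plus auricular acupressure (AA) arm.

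**The concern.** In a superiority trial, a missing-data method that draws the arms together is usually cautious. In a non-inferiority trial it works in favour of the claim.

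- **LOCF** fills a missing week-16 score with a baseline, week-4 or week-12 score and treats it as observed. At baseline, randomisation makes the expected gap zero, so early leavers dilute the difference.
- **Propensity-score imputation** matches donors on the chance of being missing, not on MRS. If donors are pooled, an AA leaver can receive a Climen patient's value, and the reverse.

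These two analyses are the only stated safeguard against up to 20% missing data. If both agree with the main result, a reader will take that as support. Yet under plausible conditions both lean towards agreement, and neither asks how poorly AA leavers would have to do before the claim failed.

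**Working it through.** **Inputs from the article.** Margin 4.5, SD 10, 103 per arm, dropout 20%, 95% confidence interval, primary time point week 16. Higher MRS is worse, so the difference is AA minus Climen.

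**Inputs assumed.** Non-inferiority is declared when the upper 95% limit is below 4.5 (nominal error 2.5%). Dropout timing, its split by arm, the correlation between visits and the course of the gap are not in the article and are varied below.

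**The plan's own figure.** n per arm = 2·SD²·(z_α + z_0.90)²/margin².
- One-sided 5%: 200 × (1.645 + 1.282)²/20.25 = 84.6, so 85. Times 1.2 gives 102; divided by 0.8 gives 107.
- One-sided 2.5%: 200 × (1.960 + 1.282)²/20.25 = 103.8, so 104 before any dropout.

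The stated 103 is within one patient of two of these. That is enough to take margin 4.5 and SD 10 as the working figures. How dropout was added is a separate matter.

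**LOCF, closed form.** Let d be the share missing at week 16, equal in both arms, and c the carried gap as a fraction of the true gap.
- Expected gap = 4.5 × [(1 − d) + d·c]
- SE = 10 × √(2/103) = 1.39
- False non-inferiority = Φ((4.5 − gap)/SE − 1.96)

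| d | c | Expected gap | False non-inferiority |
|---|---|---|---|
| 20% | 0 | 3.60 | 9.4% |
| 20% | 0.5 | 4.05 | 5.1% |
| 20% | 1 | 4.50 | 2.5% |
| 20% | 1.5 | 4.95 | 1.1% |
| 10% | 0 | 4.05 | 5.1% |
| 5% | 0 | 4.27 | 3.6% |

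First row: 4.5 × 0.8 = 3.60; (4.5 − 3.60)/1.39 = 0.65; Φ(0.65 − 1.96) = 9.4%. If the nominal level is one-sided 5%, the four 20% rows become 15.9%, 9.3%, 5.0% and 2.5%.

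**Simulation.** 400 trials per scenario, true week-16 gap 4.5, visit correlation 0.6, covariance analysis on baseline, 10 imputations, donors drawn within propensity strata by approximate Bayesian bootstrap. Each cell gives the mean estimated gap and the false non-inferiority rate. Monte Carlo standard error is about 0.8 percentage points at a rate of 2.5% and √(0.078 × 0.922/400) = 1.3 points at 7.8%.

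| Scenario (gap at weeks 4, 12, 16) | LOCF | Propensity, arm ignored | Propensity, within arm |
|---|---|---|---|
| 20% each arm, even timing (1.5, 4, 4.5) | 3.92; 7.8% | 3.59; 5.5% | 4.45; 2.2% |
| 20% each arm, mostly early (1.5, 4, 4.5) | 3.76; 11.2% | 3.63; 5.2% | 4.51; 1.5% |
| 20% each arm, mostly late, fading (3, 8, 4.5) | 4.85; 1.8% | 3.70; 6.0% | 4.47; 3.5% |
| AA 30%, Climen 10% (1.5, 4, 4.5) | 4.33; 3.8% | 3.61; 5.2% | 4.53; 2.2% |
| AA 10%, Climen 30% (1.5, 4, 4.5) | 3.61; 13.2% | 3.61; 5.8% | 4.47; 2.5% |

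With arm only as a covariate in the score, the gap ranges from 3.67 to 4.27 and the rate from 2.5% to 6.2%.

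Hand check of the LOCF column:
- Row 1: 0.8 × 4.5 + 0.2 × (0 + 1.5 + 4)/3 = 3.97, against 3.92 simulated.
- Row 3 (dropout split 10/20/70% over the three intervals): 3.6 + 0.2 × (0.2 × 3 + 0.7 × 8) = 4.84, against 4.85.

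**Is imputation itself the cause?** A second simulation (800 trials per scenario, gaps that grow to or level off at week 16) gave 4.5 and 1.9–2.8% for regression-based imputation using group and all earlier MRS values. It gave 3.9–4.0 and 5.6–6.5% for LOCF, and 4.0–4.1 and 4.0–5.9% for a propensity score containing group and baseline only. The regression model was given more visits than the score, so the last comparison is not like for like. It does show that imputation need not dilute the gap.

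**The case against.** Four stronger readings are tempting, and the article does not support them.

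1. **Both methods always pull the arms together.** Week 16 is four weeks off treatment, and the Discussion cites a study in which acupuncture did better than hormone therapy during a 6-month follow-up. A Climen advantage that fades after week 12 is therefore plausible. LOCF then carries a larger gap forward and is conservative (4.85 and 1.8% above). Propensity imputation within arm does not dilute at all. A condensed article may leave the handling of arm to the full analysis plan, so pooling of donors cannot be asserted.
2. **The trial's own false-positive risk rises.** Both methods are sensitivity analyses, not the decision test. In the simulations an analysis of observed week-16 values stayed at a gap of about 4.5, with dropout independent of outcome.
3. **The main test discards the earlier visits of patients who leave.** The sentence "A two-sided test is applied for available data" stands in the paragraph on the exploratory analysis, while the primary analysis is separately tied to the intention-to-treat population. Applying that sentence to the primary test is an inference.
4. **The two analyses cannot test robustness.** They rest on different assumptions and carry some information. What they lack is a deliberate push in the adverse direction.

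The size is also conditional: the 20% is a sample-size allowance in a study that follows patients to week 36, and less may be missing at week 16.

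All of this stands, and it limits direction and size. It does not remove the point that the article commits to LOCF and propensity-score imputation by name, that each can favour the claim, and that neither is built to oppose it.

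**Conclusion.** The point holds in conditional form: the named sensitivity analyses can bias towards non-inferiority, and neither is designed to be adverse to AA.

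With a true difference of 4.5, a nominal 2.5% level and all 20% dropout before week 16, equal in both arms, LOCF gives about 5–9% when between half and none of the gap is carried forward. With only 5–10% missing by week 16, its worst case is about 3.6–5.1%. Rates above 9% arose in simulation only with mostly early dropout or with heavier dropout in the Climen arm. Propensity imputation with pooled donors gives about 5–6%, and within arm it stays near nominal. The rates describe the sensitivity analyses alone.

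This should be changed, because the weakness affects how much trust the robustness checks deserve. It does not by itself invalidate the primary analysis.

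**What to change.** In Statistical analysis, replace LOCF and propensity-score imputation with one of the following:

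- a repeated-measures mixed model on all post-baseline MRS visits, from which the week-16 difference is estimated; or
- regression-based multiple imputation, run separately by arm, using baseline and all earlier MRS values.

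Then add a delta (tipping-point) analysis that worsens the imputed AA values only, in steps up to the 4.5 margin and on to the point where non-inferiority is lost. With 20% of AA values imputed, a penalty of 4.5 moves the estimated difference by 0.20 × 4.5 = 0.9 points against AA, so the test has real force.

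The cost is some programming and a sensitivity result that may be less favourable. No new data are needed, since MRS is already collected at every visit involved.

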The total observation period within this study is 37 weeks, including 1 week of baseline, 12 weeks of treatment and 24 weeks of follow-up. After randomization, participants will receive 28 sessions of acupuncture over a period of 12 weeks plus auricular acupressure or take Climen® (from Bayer Healthcare Company Limited, Guangzhou, China) tablets for three cycles. Acupuncture will be given as three sessions weekly in the first 4 weeks and two sessions weekly in the following 8 weeks for each patient. Each session will last 30 minutes. The follow-up period will last 24 weeks (13 to 36 weeks after randomization). Patients will be assessed before randomization as well as 4, 12, 16, 24 and 36 weeks after randomization.

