### Outcome measurement

The primary outcome of this trial is the MRS, which is widely used for evaluating the severity of aging symptoms. Eleven questions of the MRS can be classified into three categories: psychological, somatic, and urogenital. A higher score indicates worse symptoms. The primary outcome is measured at randomization and another five points (4, 12, 16, 24, and 36 weeks after randomization). The secondary outcomes include the following items: Menopause-Specific Quality of Life; average hot-flash score during 24 hours; and the level of estradiol, follicle-stimulating hormone, and luteinizing hormone in serum. The first two secondary outcomes are measured at randomization and 4, 12, 16, 24, and 36 weeks after randomization. The other secondary outcomes are measured before randomization and 12 and 24 weeks after randomization.

All patients are asked to fill in a 7-day hot flash diary before randomization and 4, 12, 16, 24, and 36 weeks after randomization. After treatment, patients will be encouraged to finish these diaries by short messages, telephone calls, and emails in order to avoid selective loss to follow-up.

To exclude patients who have serious heart, liver, and kidney diseases, all participants will also receive routine tests of blood, liver function, kidney function, and electrocardiogram before randomization. Patients will also receive breast ultrasound and gynecological B ultrasound to exclude some uncovered galactophore and gynecological diseases. Meanwhile, aiming to evaluate the side effects of both methods, participates will receive the following items after the end of treatment: breast ultrasound and gynecological B ultrasound; and liver function (alanine aminotransferase, aspartate aminotransferase) and kidney function (blood urea nitrogen, serum creatinine).

This study will also estimate the expectations of participants using the credibility and expectancy questionnaire, aiming to clarify whether expectations make an impact on outcomes.

All patients in this study are required to document whether or not they take other medicine to relieve their perimenopause-related symptoms during 36 weeks, including the name and dosage of the medicine, the time and duration of taking, the reasons and the side effects of the medicine.

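### Carrying the last MRS forward to week 16 is a poor robustness check for non-inferiority, because its bias depends on who leaves, from which arm, and when

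*Protocol article*

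**What the plan says.** The Statistical analysis section names the endpoint to be checked: "Sensitivity analyses are performed for the primary outcomes (MRS measured 16 weeks after randomization". It names two methods, "replacing missing data with multiple imputations and lost observations carried forward". I read 'lost' as 'last', that is, last observation carried forward. On the first method it adds: "Multiple imputations are calculated using the propensity score method". The analysed set is also stated: "The tests of outcomes are based on the intention-to-treat population".

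The section on study population and sample size makes the comparison non-inferiority, with a margin of 4.5 MRS points, SD 10 and power 90%. It adds: "Each group needs 103 patients (assuming a 20% dropout rate". The dropout is not split by arm or by time.

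On visits, the Outcome measurement section says: "The primary outcome is measured at randomization and another five points (4, 12, 16, 24, and 36 weeks after randomization". The Study design section gives the observation period as "including 1 week of baseline, 12 weeks of treatment and 24 weeks of follow-up".

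**The concern.** Before week 16 the MRS is taken at randomization, week 4 and week 12. Carry-forward therefore assigns scores as follows:

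- lost before week 4: the baseline score, where randomised arms do not differ in expectation;
- lost between weeks 4 and 12: a week-4 score, taken a third of the way through treatment;
- lost between weeks 12 and 16: a week-12 score, taken at the end of treatment. Both treatments last 12 weeks (three 28-day Climen cycles are 84 days), so week 16 is off treatment in both arms.

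The method assumes that nothing changes after the last visit attended. The article's Discussions section gives reason to doubt this. It cites one trial in which acupuncture kept relieving vasomotor symptoms through three months, and another in which acupuncture did better than hormone therapy during six months of follow-up.

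In a superiority trial, pulling the arms together is often tolerated as conservative. In a non-inferiority trial it favours the claim. At stake is how the check would be read: if carry-forward agreed with the main analysis, that agreement would be reported as robustness.

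**Working it through.** **Inputs.** From the article: margin 4.5, SD 10, 103 per arm, 20% dropout, MRS visits at 0, 4, 12 and 16 weeks, two-sided testing at 0.05 (one-sided 0.025 against the margin). Assumed, because the article does not give them: timing and arm split of dropout, how the difference builds over visits, and correlations between visits.

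**The plan's own figure.** With no true difference and one-sided 0.05, n = 2 × (10 × (1.645 + 1.282)/4.5)² = 84.6, so 85 per arm. Then 85 × 1.2 = 102, and the t-based 86 × 1.2 = 103.2. One-sided 0.025 gives 104 with no dropout allowance. The inputs are therefore the plan's own. How the 103 was reached is a separate matter and does not affect this point.

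**Equal 20% dropout in both arms, acupuncture truly worse by 4.5 at week 16.** Let f0, f4 and f12 be the fractions whose last score is at baseline, week 4 and week 12, and D4 and D12 the true differences at those visits. The expected carry-forward estimate is

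E = 0.8 × 4.5 + f0 × 0 + f4 × D4 + f12 × D12.

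Unadjusted SE = 10 × √(2/103) = 1.393. The chance that the upper 95% limit falls below 4.5 is Φ((4.5 − E)/1.393 − 1.96).

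| Difference at weeks 0/4/12/16 | f0/f4/f12 (%) | E | False non-inferiority |
|---|---|---|---|
| any | 20/0/0 | 3.60 | 9.4% |
| 0/1/3/4.5 | 7/8/5 | 3.6 + 0.08 + 0.15 = 3.83 | 7.0% |
| 0/2/4.5/4.5 | 7/8/5 | 3.6 + 0.16 + 0.225 = 3.99 | 5.6% |
| 0/4.5/4.5/4.5 | 7/8/5 | 3.6 + 0.36 + 0.225 = 4.19 | 4.1% |
| 0/2/4.5/4.5 | 5/5/10 | 3.6 + 0.10 + 0.45 = 4.15 | 4.4% |

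Simulating these three profiles with each dropout split (4,000 trials each, correlations 0.5 to 0.8) gave estimates of 3.59 to 4.25 and false non-inferiority of 3.95% to 12.8%. A second simulation (10,000 trials each, ANCOVA on baseline MRS, correlation 0.5) gave 8.5-8.7% when all leave before week 12 and about 6% when leaving is spread to week 16. With no dropout it gave 2.4-2.5%, as it should. The simulated rates can exceed the table because adjusting for baseline narrows the interval. At correlation 0.5 and ignoring dropout, the SE is 1.393 × √0.75 = 1.207, and (4.5 − 3.6)/1.207 − 1.96 gives 11.2%.

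**Late dropout only (all 20% lost between weeks 12 and 16).** E = 0.8 × 4.5 + 0.2 × D12.

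- D12 = 4.5: E = 4.5, rate 2.5%, no bias.
- D12 = 6: E = 4.8, rate 1.5%.
- D12 = 7: E = 5.0, rate 1.0%.

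If the difference shrinks after week 12, late carry-forward thus works against acupuncture. It need not do so when dropout is mixed: with 0/2/6/4.5 and the 7/8/5 split, E = 3.6 + 0.16 + 0.30 = 4.06, still below 4.5.

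**Unequal dropout, all leavers carrying baseline.** With assumed improvements of 6.5 on Climen and 2 on acupuncture:

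- acupuncture 10%, Climen 30%: 6.5 × 0.7 − 2 × 0.9 = 2.75, rate 24%;
- acupuncture 30%, Climen 10%: 6.5 × 0.9 − 2 × 0.7 = 4.45, rate 2.7%.

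The simulation, with half of the leavers carrying a week-4 score and Climen improvements of 6.5 to 10, gave 22-35% for the first split and 1.0-2.7% for the second.

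**An adverse shift, for comparison.** With 20% missing in the acupuncture arm, worsening each imputed score by δ moves the estimate by 0.2 × δ: 0.2 for one point, 0.9 for 4.5 points. At a true difference of zero, the 0.9 shift lowers the chance of showing non-inferiority from 89.8% to about 73% (one-sided 0.025).

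**The case against.** The strongest reply is that carry-forward is only a sensitivity analysis, listed beside multiple imputation, and that its direction is not known. Acupuncture requires 28 clinic visits against tablets at home, and the article itself links treatment demand to dropout. Losses could well be heavier in the acupuncture arm, where carry-forward is roughly neutral or works against acupuncture. The figure near 13% comes from the extreme case in which every leaver goes before week 4. All of this stands. It limits the size of the problem, but it also confirms the point: a check whose bias can run either way with an unknown dropout pattern cannot show robustness.

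Three stronger readings are tempting, and the document does not support them.

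- A reader might infer that carry-forward always makes the arms look alike. It does so with similar early dropout. The late and unequal cases above show otherwise.
- A reader might infer that the trial has no analysis adverse to acupuncture. The article states none, but it is a condensed account. The full protocol and analysis plan are not shown, so silence here is no finding.
- A reader might take 4-13% as the trial's false-positive rate. It is the rate for carry-forward read alone. No joint rate with the main analysis or multiple imputation was computed.

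One could also keep carry-forward and interpret it cautiously. That would do no harm, but it would leave a check that tells the reader nothing about the direction that matters.

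**Conclusion.** The concern holds in limited form. The article fixes carry-forward as one of two named missing-data checks on week-16 MRS in a non-inferiority comparison, and the method can support a false claim. With 20% early dropout similar in both arms, a true difference of 4.5 is estimated at about 3.6 to 4.2. Carry-forward alone then shows false non-inferiority in roughly 4-13% of trials instead of 2.5%. These figures rest on assumed dropout timing, growth of the difference and visit correlations. Other patterns, equally open under the article, give no bias or the opposite bias. The defect is a badly chosen check, not a demonstrated error in the trial's conclusion, and it should be changed because the change is cheap.

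**What to change.** Replace carry-forward with a delta-adjusted tipping-point analysis built on the multiple imputation already planned. Suggested content: after imputing week-16 MRS, add δ = 1, 2, ... points to the imputed scores in the acupuncture arm only, refit the planned analysis of covariance, and pool. Report the δ at which the upper 95% confidence limit for acupuncture minus Climen crosses 4.5, and whether a shift of that size is plausible. Report the number and timing of losses by arm beside it.

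The result is easy to read. With an observed difference of 0 and SE 1.393, the upper limit is 1.96 × 1.393 = 2.73. The slack is 4.5 − 2.73 = 1.77, so δ is about 1.77/0.2 = 8.8 points. With an observed difference of 1, the slack is 0.77 and δ is about 3.8 points. Both figures assume 20% missing and ignore the extra variance from imputation, which would lower them.

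Cost: a change of wording and a few extra runs, with no new data. The downside is that the conclusion may look less robust than agreement with carry-forward would have suggested.

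### If donors are pooled across arms, the propensity-score imputation in the week-16 MRS sensitivity analysis shrinks a true acupuncture deficit; run within arms, it only loses precision

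*Protocol article*

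**What the plan says.** The Statistical analysis section of the protocol article bases the outcome tests on randomised patients: "The tests of outcomes are based on the intention-to-treat population". The model is an analysis of covariance (ANCOVA) "with baseline MRS and age as covariates", reported with 95% confidence intervals.

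Missing data come in at a second level: "Sensitivity analyses are performed for the primary outcomes (MRS measured 16 weeks after randomization) by replacing missing data with multiple imputations", alongside a carry-forward analysis. One further sentence fixes the imputation method: "Multiple imputations are calculated using the propensity score method". The variables in the score are not listed, and nothing is said about imputing by arm.

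The Study population and sample size section sets the frame: "we assume that a difference within 4.5 indicates acupuncture is not inferior to Climen® treatment". Under Outcome measurement, a higher MRS means worse symptoms, so a true AA deficit is a positive AA minus Climen difference.

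**The concern.** The propensity score method models the probability that the week-16 score is missing, sorts patients into strata of that probability, and fills each gap with an observed score drawn from the same stratum. Baseline MRS, earlier MRS and arm enter only as far as they predict missingness, not as predictors of the week-16 score.

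When the arms drop out at similar rates, the strata do not separate them. Unless imputation is run by arm, missing AA patients then receive scores partly from Climen patients, and the reverse, which pulls the arms together. In a non-inferiority comparison that pull favours success when AA is truly worse. A sensitivity analysis should test whether the main result survives missing data; one that draws the arms together can agree with a favourable result for the wrong reason.

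**Working it through.** **Inputs from the article.** Margin 4.5; "assuming a power of 90%, an alpha value of 5%, and a population standard deviation of 10"; 103 per arm with 20% dropout; 1:1 allocation; ANCOVA on baseline MRS and age.

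**Assumptions not in the article.** Baseline to week-16 correlation 0.5; where week-12 MRS is used, correlations of 0.5 with baseline and 0.7 with week 16; the share missing at week 16; five strata with an approximate Bayesian bootstrap; Rubin's rules; non-inferiority declared when the upper 95% limit is below 4.5.

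**1. The plan's own figure.** Per arm, n = 2 × SD² × (z for alpha + z for power)² / margin².
- One-sided 5%: 200 × (1.645 + 1.282)² / 20.25, rounded up to 85. Then 85 × 1.2 = 102, close to the stated 103; 85 / 0.8 gives 107.
- One-sided 2.5%: 104 before any dropout allowance, and 104 / 0.8 = 130 after it.

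So 103 is reproduced approximately, and 103 per arm is used below.

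**2. Expected shrinkage when donors are pooled.** Let the true difference be d and the missing share p in both arms. About half the donors come from each arm, so imputed values average d/2 above the Climen mean in either arm. The AA mean becomes (1 − p)d + pd/2 and the Climen mean pd/2. The difference is d(1 − p). With d = 4.5 this gives 4.05 at 10% missing, 3.60 at 20% and 3.15 at 30%.

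**3. Simulation with baseline MRS and age only** (2000 runs, 20 imputations, true deficit 4.5). Each cell shows the mean estimate and the false non-inferiority rate at nominal 2.5%.

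| Missingness | Pooled, arm not in score | Pooled, arm in score | Within arm | Regression |
|---|---|---|---|---|
| 10%, at random | 4.06; 3.6% | 4.18; 3.8% | 4.46; 2.4% | 4.48; 2.2% |
| 20%, at random | 3.63; 4.4% | 3.85; 4.9% | 4.52; 3.0% | 4.47; 2.7% |
| 30%, at random | 3.16; 7.3% | 3.59; 7.2% | 4.44; 3.4% | 4.53; 2.4% |
| 20%, by baseline MRS | 3.53; 5.6% | 3.67; 6.4% | 4.54; 2.0% | 4.49; 2.5% |
| 20%, by baseline MRS and arm | 3.53; 6.2% | 4.38; 1.8% | 4.53; 2.6% | 4.50; 2.2% |

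'At random' here means completely at random. The pooled means without arm in the score follow step 2. Complete-case ANCOVA at 20% completely at random gives 4.47 and 2.8%. Simulation error is about 0.35 percentage points at 2.5% (√(0.025 × 0.975 / 2000)) and about 0.5 at 5%.

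**4. Simulation with week-12 MRS and arm in the score** (5000 runs, 10 imputations, 20% missing). Each cell shows the mean estimate, the average standard error and the false non-inferiority rate.

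| Missingness | Pooled | Within arm | Regression |
|---|---|---|---|
| Completely at random | 3.81; 1.42; 5.6% | 4.49; 1.42; 2.0% | 4.50; 1.32; 2.4% |
| By baseline MRS | 3.66; 1.38; 6.0% | 4.50; 1.40; 2.4% | 4.49; 1.32; 2.8% |
| By week-12 MRS | 4.03; 1.35; 4.2% | 4.46; 1.38; 2.3% | 4.48; 1.32; 2.5% |

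Within-arm against regression standard errors: 1.42/1.32 = 1.08, 1.40/1.32 = 1.06, 1.38/1.32 = 1.05, so 5% to 8% wider.

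**5. A third simulation at 20% missing** gave pooled estimates of about 3.5 to 3.9, and false non-inferiority of about 5% to 8% against 2.2% to 2.6% with regression imputation. Within arms there was no bias, and the standard error was about 6% to 8% wider.

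**6. Unequal dropout.** With 10% missing in AA and 30% in Climen, arm in the score and donors pooled (1200 runs), the estimate is 4.3, and power at a true difference of zero is 86% against 91%. The last row of the table in step 3 shows that this protection needs arm in the score: 4.38 and 1.8% with it, 3.53 and 6.2% without.

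**The case against.** The strongest reply is that the bias comes from pooling, and the article never says donors are pooled. It is a condensed report; the variables in the score and whether imputation runs by arm are details that an analysis plan usually settles. Within arms, the simulations show neither shrinkage nor inflation. This stands, and it makes the bias conditional. It does not clear the named method, which is less precise within arms because it makes little use of how other MRS visits predict week 16.

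Second, a reader might infer that the trial's own false non-inferiority rate doubles. The article does not support that: it places the imputation among sensitivity analyses, next to carry-forward, and the outcome tests do not rest on it.

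Third, 20% missing at week 16 may be too high. The 20% is a dropout figure for the whole study, and the Discussions section ties dropout to the full 37 weeks. At 10% missing the inflation is smaller. Unequal dropout is also plausible with 28 clinic visits in one arm and tablets in the other. Both points stand as limits on size.

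Fourth, it would be too strong to say that the method ignores symptoms. A score containing baseline and week-12 MRS sorts patients partly by symptoms when missingness depends on them, and shrinkage in step 4 is then smallest (4.03). The ANCOVA also still adjusts for baseline.

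Finally, patients who have left by week 16 will usually lack weeks 24 and 36. The later visits therefore help mainly where single visits are missed, and the fix asks only for observed visits.

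**Conclusion.** The point holds in conditional form. The article names an imputation method that is biased toward non-inferiority under one reading and less precise under the other.

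- **Pooled across arms, similar dropout, 20% missing:** a true deficit of 4.5 is estimated at about 3.5 to 4.0, and false non-inferiority in the sensitivity analysis is about 4% to 8% instead of about 2.5%. At 10% missing it is about 3.6%.
- **Pooled, clearly unequal dropout, arm in the score:** no inflation, with some loss of power in the case examined.
- **Within arms:** unbiased, with a standard error about 5% to 8% wider than regression imputation when week-12 MRS is available.

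The error rates assume that the upper 95% limit is compared with 4.5, a rule that the Statistical analysis section does not state. The correlations and missing shares are also assumed. The consequence is false reassurance about robustness, not a changed error rate for the main test.

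**What to change.** Replace the sentence on the propensity score method with: *Missing week-16 MRS is multiply imputed by regression or predictive mean matching, separately in each arm, from baseline MRS, age and the other observed MRS visits; the stated ANCOVA is combined by Rubin's rules.*

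If the propensity score method is kept, the text should at the least say that it is run within each arm. That removes the bias shown above but not the loss of precision.

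The cost is one sentence. The MRS visits are already scheduled, so no new data or visits are needed, and the article reports that the trial is still recruiting.
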